### **8.3 Other data related to safety**

Vital signs (systolic and diastolic blood pressure, pulse rate, respiratory rate) will be summarised by treatment and time point, including changes from Day 0 (pre-dose) with the number of observations, mean, standard deviation, median, quartiles, minimum and maximum. Vital signs measured in any position (sitting, supine, standing) will be combined for the summary tables.

## **9. LIST OF TABLES AND FIGURES**

*see Section 12*

## **10. LIST OF DATA LISTINGS AND STATISTICAL TABULATIONS**

*see Section 12*

## **12. TABLE SHELLS**

**Table 2.7.4-1 Patient disposition and exposure**  
**Paediatric safety population**  
 (Page 1 of 1)

|                                      | Pyronaridine
artesunate | Artemether
lumefantrine | Total       |
|--------------------------------------|----------------------------|----------------------------|-------------|
| Patients treated (at least one dose) | xxx (100.0)                | xxx (100.0)                | xxx (100.0) |
| Patients who completed study         | xxx (xx.x)                 | xxx (xx.x)                 | xxx (xx.x)  |
| Reason for withdrawal                |                            |                            |             |
| Treatment failure                    | xxx (xx.x)                 | xxx (xx.x)                 | xxx (xx.x)  |
| Adverse event                        | xxx (xx.x)                 | xxx (xx.x)                 | xxx (xx.x)  |
| Death                                | xxx (xx.x)                 | xxx (xx.x)                 | xxx (xx.x)  |
| Protocol violation                   | xxx (xx.x)                 | xxx (xx.x)                 | xxx (xx.x)  |
| Lost to follow-up                    | xxx (xx.x)                 | xxx (xx.x)                 | xxx (xx.x)  |
| Withdrawal of consent                | xxx (xx.x)                 | xxx (xx.x)                 | xxx (xx.x)  |
| Pregnancy                            | xxx (xx.x)                 | xxx (xx.x)                 | xxx (xx.x)  |
| Study terminated by Sponsor          | xxx (xx.x)                 | xxx (xx.x)                 | xxx (xx.x)  |
| Other                                | xxx (xx.x)                 | xxx (xx.x)                 | xxx (xx.x)  |

Note: Percentages are based on the number of randomised patients.

For SP-C-013-11 a patient was considered to have completed if the first treatment episode was completed.

**Table 2.7.4-2**      **Demographic characteristics**  
**Paediatric safety population**  
**(Page 1 of 3)**

| Variable/
Statistic/Category | Pyronaridine
artesunate
(N=xxx) | Artemether
lumefantrine
(N=xxx) |
|---------------------------------|---------------------------------------|---------------------------------------|
| Gender, n (%)                   |                                       |                                       |
| Male                            | xxx (xx.x)                            | xxx (xx.x)                            |
| Female                          | xxx (xx.x)                            | xxx (xx.x)                            |
| Age (years)                     |                                       |                                       |
| Available observations          | xxx                                   | xxx                                   |
| Mean                            | xx.x                                  | xx.x                                  |
| Standard deviation              | x.xx                                  | x.xx                                  |
| Minimum                         | xx                                    | xx                                    |
| Q1                              | xx.x                                  | xx.x                                  |
| Median                          | xx                                    | xx                                    |
| Q3                              | xx.x                                  | xx.x                                  |
| Maximum                         | xx                                    | xx                                    |
| Age category, n (%)             |                                       |                                       |
| <=6 months                      | xxx (xx.x)                            | xxx (xx.x)                            |
| >6 months - <1 year             | xxx (xx.x)                            | xxx (xx.x)                            |
| 1-2 years                       | xxx (xx.x)                            | xxx (xx.x)                            |
| 3-5 years                       | xxx (xx.x)                            | xxx (xx.x)                            |
| >=6 years                       | xxx (xx.x)                            | xxx (xx.x)                            |

Missing values were not included in the calculation of percentages.

**Table 2.7.4-2**      **Demographic characteristics**  
**Paediatric safety population**  
**(Page 2 of 3)**

| Variable/
Statistic/Category | Pyronaridine
artesunate
(N=xxx) | Artemether
lumefantrine
(N=xxx) |
|---------------------------------|---------------------------------------|---------------------------------------|
| Height (cm)                     |                                       |                                       |
| Available observations          | xxx                                   | xxx                                   |
| Mean                            | xxx.x                                 | xxx.x                                 |
| Standard deviation              | xx.xx                                 | xx.xx                                 |
| Minimum                         | xxx                                   | xxx                                   |
| Q1                              | xxx                                   | xxx                                   |
| Median                          | xxx.x                                 | xxx.x                                 |
| Q3                              | xxx                                   | xxx                                   |
| Maximum                         | xxx                                   | xxx                                   |
| Body weight (kg)                |                                       |                                       |
| Available observations          | xxx                                   | xxx                                   |
| Mean                            | xx.x                                  | xx.x                                  |
| Standard deviation              | x.xx                                  | x.xx                                  |
| Minimum                         | xx.x                                  | xx.x                                  |
| Q1                              | xx.x                                  | xx.x                                  |
| Median                          | xx.x                                  | xx.x                                  |
| Q3                              | xx.x                                  | xx.x                                  |
| Maximum                         | xx.x                                  | xx.x                                  |

Missing values were not included in the calculation of percentages.

**Table 2.7.4-2**      **Demographic characteristics**  
**Paediatric safety population**  
**(Page 3 of 3)**

| Variable/
Statistic/Category | Pyronaridine
artesunate
(N=xxx) | Artemether
lumefantrine
(N=xxx) |
|---------------------------------|---------------------------------------|---------------------------------------|
| Body weight category, n (%)     |                                       |                                       |
| <8 kg                           | xxx (xx.x)                            | xxx (xx.x)                            |
| 8 - <15 kg                      | xxx (xx.x)                            | xxx (xx.x)                            |
| 15 - <20 kg                     | xxx (xx.x)                            | xxx (xx.x)                            |
| Body mass index (kg/m**2)       |                                       |                                       |
| Available observations          | xxx                                   | xxx                                   |
| Mean                            | xx.xx                                 | xx.xx                                 |
| Standard deviation              | x.xxx                                 | x.xxx                                 |
| Minimum                         | xx.x                                  | xx.x                                  |
| Q1                              | xx.xx                                 | xx.xx                                 |
| Median                          | xx.xx                                 | xx.xx                                 |
| Q3                              | xx.xx                                 | xx.xx                                 |
| Maximum                         | xx.x                                  | xx.x                                  |

Missing values were not included in the calculation of percentages.

**Table 2.7.4-3 Study drug exposure**  
**Paediatric safety population**  
**(Page 1 of 1)**

| Variable/
Category          | Pyronaridine
artesunate
(N=xxx) |        | Artemether
lumefantrine
(N=xxx) |        |
|--------------------------------|---------------------------------------|--------|---------------------------------------|--------|
|                                | n                                     | (%)    | n                                     | (%)    |
| Total number of doses taken *  |                                       |        |                                       |        |
| One                            | xxx                                   | (xx.x) | xxx                                   | (xx.x) |
| Two                            | xxx                                   | (xx.x) | xxx                                   | (xx.x) |
| Three                          | xxx                                   | (xx.x) | xxx                                   | (xx.x) |
| Four                           | xxx                                   | (xx.x) | xxx                                   | (xx.x) |
| Five                           | xxx                                   | (xx.x) | xxx                                   | (xx.x) |
| Six                            | NA                                    |        | xxx                                   | (xx.x) |
| Seven                          | NA                                    |        | xxx                                   | (xx.x) |
| Eight                          | NA                                    |        | xxx                                   | (xx.x) |
| Dose repeated                  |                                       |        |                                       |        |
| Day 0 - Dose 1                 | xx                                    | (xx.x) | xx                                    | (xx.x) |
| Day 0 - Dose 2                 | NA                                    |        | xx                                    | (xx.x) |
| Day 1 - Dose 1                 | xx                                    | (xx.x) | xx                                    | (xx.x) |
| . . .                          |                                       |        |                                       |        |
| Dose vomited within 30 minutes |                                       |        |                                       |        |
| Day 0 - Dose 1                 | xxx                                   | (xx.x) | xxx                                   | (xx.x) |
| Repeated dose                  | xxx                                   | (xx.x) | xxx                                   | (xx.x) |
| Day 0 - Dose 2                 | NA                                    |        | xxx                                   | (xx.x) |
| Repeated dose                  | NA                                    |        | xxx                                   | (xx.x) |
| . . .                          |                                       |        |                                       |        |

NA = not applicable

\* Original and repeat doses were taken into account.

**Table 2.7.4-4 Study drug dosage**  
**Paediatric safety population**  
**(Page 1 of 1)**

| Variable/
Statistic | Pyronaridine
artesunate
(N=xxx) | Artemether
lumefantrine
(N=xxx) |
|------------------------|---------------------------------------|---------------------------------------|
| mg/kg                  | Artesunate                            | Artemether                            |
| Available observations | xxx                                   | xxx                                   |
| Mean                   | x.xx                                  | x.xx                                  |
| SD                     | x.xxx                                 | x.xxx                                 |
| Minimum                | x.xx                                  | x.xx                                  |
| Q1                     | x.xx                                  | x.xx                                  |
| Median                 | x.xx                                  | x.xx                                  |
| Q3                     | x.xx                                  | x.xx                                  |
| Maximum                | x.xx                                  | x.xx                                  |
| mg/kg                  | Pyronaridine                          | Lumefantrine                          |
| Available observations | xxx                                   | xxx                                   |
| Mean                   | x.xx                                  | x.xx                                  |
| SD                     | x.xxx                                 | x.xxx                                 |
| Minimum                | x.xx                                  | x.xx                                  |
| Q1                     | x.xx                                  | x.xx                                  |
| Median                 | x.xx                                  | x.xx                                  |
| Q3                     | x.xx                                  | x.xx                                  |
| Maximum                | x.xx                                  | x.xx                                  |

Note: Original and repeat doses were taken into account.

**Table 2.7.4-5**      **Overview of adverse events, by treatment**  
**Paediatric safety population**  
**(Page 1 of 1)**

| Number (%) of patients with                  | Pyronaridine
artesunate |         | Artemether
lumefantrine |         | p-value |
|----------------------------------------------|----------------------------|---------|----------------------------|---------|---------|
|                                              | n                          | (%)     | n                          | (%)     |         |
| Number of patients dosed                     | xxx                        | (100.0) | xxx                        | (100.0) |         |
| Any adverse event                            | xxx                        | (xx.x)  | xxx                        | (xx.x)  | 0.xxxx  |
| Any drug-related adverse event *             | xxx                        | (xx.x)  | xxx                        | (xx.x)  | 0.xxxx  |
| Any serious adverse event                    | xxx                        | (xx.x)  | xxx                        | (xx.x)  | 0.xxxx  |
| Any serious drug-related adverse event *     | xxx                        | (xx.x)  | xxx                        | (xx.x)  | 0.xxxx  |
| Any severe or life-threatening adverse event | xxx                        | (xx.x)  | xxx                        | (xx.x)  | 0.xxxx  |
| Any adverse event leading to death           | xxx                        | (xx.x)  | xxx                        | (xx.x)  | 0.xxxx  |

Note: \* Drug-related = possible, probable, definite or missing relationship to study drug.  
p-values from Fisher's exact test for the difference between PA and AL.

**Table 2.7.4-6 Incidence of all adverse events by MedDRA primary system organ class and preferred term  
Paediatric safety population  
(Page 1 of n)**

| Primary system organ class   | Pyronaridine
artesunate | Artemether
lumefantrine |         |
|------------------------------|----------------------------|----------------------------|---------|
| Preferred term               | n (%)                      | n (%)                      | p-value |
| Patients dosed               | xxx (100.0)                | xxx (100.0)                |         |
| At least one adverse event   | xxx (xx.x)                 | xxx (xx.x)                 | 0.xxxx  |
| Primary system organ class 1 | xxx (xx.x)                 | xxx (xx.x)                 | 0.xxxx  |
| Preferred term 1             | xxx (xx.x)                 | xxx (xx.x)                 | 0.xxxx  |
| Preferred term 2             | xxx (xx.x)                 | xxx (xx.x)                 | 0.xxxx  |
| Primary system organ class 2 | xxx (xx.x)                 | xxx (xx.x)                 | 0.xxxx  |
| Preferred term 1             | xxx (xx.x)                 | xxx (xx.x)                 | 0.xxxx  |
| Preferred term 2             | xxx (xx.x)                 | xxx (xx.x)                 | 0.xxxx  |
| etc.                         |                            |                            |         |

A patient with more than one adverse event within a primary system organ class is counted only once for that class.  
p-values from Fisher's exact test for the difference between PA and AL.

**Table 2.7.4-7**      **Incidence of adverse events considered to be study drug related, by MedDRA primary system organ class and preferred term**  
**Paediatric safety population**

*Programming note: Same layout as Table 2.7.4-6. Present only AEs that were considered to be study drug-related.*

**Table 2.7.4-8**      **Incidence of serious adverse events, by MedDRA primary system organ class and preferred term**  
**Paediatric safety population**

*Programming note: Same layout as Table 2.7.4-6. Present serious AEs.*

**Table 2.7.4-9**      **Incidence of serious adverse events considered to be study drug related, by MedDRA primary system organ class and preferred term**  
**Paediatric safety population**

*Programming note: Same layout as Table 2.7.4-6. Present serious AEs that were considered to be study drug related.*

**Table 2.7.4-10**      **Incidence of all adverse events by MedDRA primary system organ class, preferred term, maximal severity**  
**Paediatric safety population**  
**(Page 1 of n)**

| Primary system organ class | Preferred term   | Maximal severity | Pyronaridine artesunate
N (%) | Artemether lumefantrine
n (%) |
|----------------------------|------------------|------------------|----------------------------------|----------------------------------|
| Patients dosed             |                  |                  | xxx (100.0)                      | xxx (100.0)                      |
| At least one AE            | Total            | Total            | xxx (xx.x)                       | xxx (xx.x)                       |
|                            |                  | Mild             | xxx (xx.x)                       | xxx (xx.x)                       |
|                            |                  | Moderate         | xxx (xx.x)                       | xxx (xx.x)                       |
|                            |                  | Severe           | xxx (xx.x)                       | xxx (xx.x)                       |
| Primary SOC 1              | Total            | Total            | xxx (xx.x)                       | xxx (xx.x)                       |
|                            |                  | Mild             | xxx (xx.x)                       | xxx (xx.x)                       |
|                            | Preferred term 1 | Total            | xxx (xx.x)                       | xxx (xx.x)                       |
|                            |                  | Moderate         | xxx (xx.x)                       | xxx (xx.x)                       |
| etc.                       |                  |                  |                                  |                                  |

If a patient reported more than one adverse event within the same category, the worst severity was summarised.

A patient with more than one adverse event within a primary system organ class is counted only once for that class.

**Table 2.7.4-11**      **Summary of ALT values (U/L) by treatment and time point**  
**Paediatric safety population**  
**(Page 1 of n)**

|                                 | Time point | N   | Mean | SD   | Minimum | Q1   | Median | Q3   | Maximum |
|---------------------------------|------------|-----|------|------|---------|------|--------|------|---------|
| Pyronaridine artesunate (N=xxx) |            |     |      |      |         |      |        |      |         |
| Raw values                      | Day 0      | xxx | xx.x | x.xx | x.xx    | x.xx | x.xx   | x.xx | x.xx    |
|                                 | Day 3      | xxx | xx.x | x.xx | x.xx    | x.xx | x.xx   | x.xx | x.xx    |
|                                 | Day 7      | xxx | xx.x | x.xx | x.xx    | x.xx | x.xx   | x.xx | x.xx    |
|                                 | Day 28     | xxx | xx.x | x.xx | x.xx    | x.xx | x.xx   | x.xx | x.xx    |
| Changes from Day 0              | Day 3      | xxx | xx.x | x.xx | x.xx    | x.xx | x.xx   | x.xx | x.xx    |
|                                 | Day 7      | xxx | xx.x | x.xx | x.xx    | x.xx | x.xx   | x.xx | x.xx    |
|                                 | Day 28     | xxx | xx.x | x.xx | x.xx    | x.xx | x.xx   | x.xx | x.xx    |
| Artemether lumefantrine (N=xxx) |            |     |      |      |         |      |        |      |         |
| Raw values                      | Day 0      | xxx | xx.x | x.xx | x.xx    | x.xx | x.xx   | x.xx | x.xx    |
|                                 | Day 3      | xxx | xx.x | x.xx | x.xx    | x.xx | x.xx   | x.xx | x.xx    |
|                                 | Day 7      | xxx | xx.x | x.xx | x.xx    | x.xx | x.xx   | x.xx | x.xx    |
|                                 | Day 28     | xxx | xx.x | x.xx | x.xx    | x.xx | x.xx   | x.xx | x.xx    |
| Changes from Day 0              | Day 3      | xxx | xx.x | x.xx | x.xx    | x.xx | x.xx   | x.xx | x.xx    |
|                                 | Day 7      | xxx | xx.x | x.xx | x.xx    | x.xx | x.xx   | x.xx | x.xx    |
|                                 | Day 28     | xxx | xx.x | x.xx | x.xx    | x.xx | x.xx   | x.xx | x.xx    |

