## 1. INTRODUCTION

This analysis plan describes the ISS analyses planned for the Pyramax paediatric (granule) formulation submission to EMA.

For the analysis of paediatric safety data the safety data of the following studies will be pooled:

- SP-C-003-05, Cohort D, patients treated with the PA granule formulation weighing <20 kg
- SP-C-007-07 (both PA and AL) weighing <20 kg
- WANECAM paediatric patients (weighing <20 kg) from the corresponding sub study analysis, treatment episode 1 only.

All analyses will be performed by DATAMAP GmbH, Freiburg, Germany using SAS®, Version 9.3 in a UNIX environment.

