## 8.2 Clinical laboratory data

Clinical laboratory data (AST, ALT, total bilirubin, direct bilirubin, if available, alkaline phosphatase, serum creatinine, haemoglobin, platelet count, white blood count, neutrophils, lymphocytes, eosinophils) will be summarised by treatment group and time point, including changes from Day 0 (pre-dose) with the number of observations, mean, standard deviation, median, quartiles, minimum and maximum.

SI values will be used for summarisation.

To evaluate potential anemia, incidence rates of patients having a hemoglobin change from baseline:

$\geq 0$  g/L,  $-20 < 0$  g/L, or  $< -20$  g/L will be summarized for each time point.

Incidence rates of liver enzyme abnormalities will be summarized by time point and for the worst (highest) value based on the following event criteria (note that criteria are not mutually exclusive):

| Parameter             | Criterion                                                                                                    |
|-----------------------|--------------------------------------------------------------------------------------------------------------|
| ALT                   | $\leq 1.5$ ULN, $> 1.5$ ULN and $\leq 3 \times$ ULN
$> 3 \times$ ULN; $> 5 \times$ ULN; $> 10 \times$ ULN |
| AST                   | $\leq 1.5$ ULN, $> 1.5$ ULN and $\leq 3 \times$ ULN
$> 3 \times$ ULN; $> 5 \times$ ULN; $> 10 \times$ ULN |
| ALT or AST            | $> 3 \times$ ULN; $> 5 \times$ ULN; $> 10 \times$ ULN                                                        |
| Total bilirubin (TBL) | $> 1.5 \times$ ULN, $> 2 \times$ ULN, $> 3 \times$ ULN                                                       |
| ALT or AST & TBL      | ALT or AST $> 3 \times$ ULN & TBL $> 2 \times$ ULN (Hy's Law)                                                |

ULN=upper limit of normal range of the local laboratory.

For a combined criterion to be fulfilled all criteria have to be fulfilled at the same time point.

Shift tables of the above categories at Day 0 versus the worst post baseline value will be generated.

The following graphical displays of liver function test data will be generated:

Comparison between treatment groups and between first and subsequent dosing using scatter plots of the peak total bilirubin value versus the peak ALT/AST values (expressed relative to the upper limit of normal) from Day 3 until Day 28 and from Day 7 until Day 28 (E-Dish graphs).

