Scatter plots for ALT, total bilirubin showing individual data by day (y axis will present value, x-axis will present Day 0, 3, 7 and 28) – separately for treatment groups for all patients and for patients who had at least one re-treatment.

ALT classifications relative to the normal ranges, incidence rates of potential liver abnormalities and shifts of ALT categories will further be summarised by body weight category.

Potential differences between PA and AL of ALT and AST classifications relative to the normal ranges will be analysed using the Chi-square test and incidence rates of potential liver abnormalities using Fisher's exact test.

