**Table 2.7.4-12**      **Summary of AST values (U/L) by treatment and time point**  
**Paediatric safety population**

*Programming note: Same layout as Table 2.7.4-11 for AST*

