**Table 2.7.4-13**      **Summary of total bilirubin values (umol/L) by treatment and time point**  
**Paediatric safety population**

*Programming note: Same layout as Table 2.7.4-11 for total bilirubin*

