**Table 2.7.4-14**      **Summary of alkaline phosphatase values (U/L) by treatment and time point**  
**Paediatric safety population**

*Programming note: Same layout as Table 2.7.4-11 for alkaline phosphatase*

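### Liver-test summary tables and over-time plots pool raw units across local laboratories, although the plan scales its other liver outputs to the local ULN

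*SAP*

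**What the plan says.** - **Continuous summaries.** Table 2.7.4-11 is titled "Summary of ALT values (U/L) by treatment and time point". It gives mean, SD, quartiles and range for raw values and for changes from Day 0, and has no p-value column. The same layout serves "Summary of AST values (U/L) by treatment and time point" (Table 2.7.4-12), "Summary of total bilirubin values (umol/L) by treatment and time point" (Table 2.7.4-13) and "Summary of alkaline phosphatase values (U/L) by treatment and time point" (Table 2.7.4-14).
- **Harmonisation.** Section 8.2 states only "SI values will be used for summarisation".
- **Over-time plots.** Section 8.2 specifies "y axis will present value, x-axis will present Day 0, 3, 7 and 28". Section 12 lists them as Figures 2.7.4-5 to -7, for ALT, AST and total bilirubin.
- **Outputs on the ULN scale.** Section 8.2 sets out liver criteria in multiples of ULN, with the note "ULN=upper limit of normal range of the local laboratory". Tables 2.7.4-16 to -18, the ALT and AST shift tables (2.7.4-19 and -20) and the E-Dish plots (Figures 2.7.4-1 to -4) use that scale. The planned liver tests, Chi-square for the ALT and AST classes and Fisher's exact test for the abnormality criteria, belong to Tables 2.7.4-16 to -18 and to their versions by body weight.
- **Sources.** Section 1 lists "SP-C-003-05, Cohort D, patients treated with the PA granule formulation weighing <20 kg" and names no AL patients from that study. SP-C-007-07 contributes both treatments.

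**The concern.** By defining ULN through the local laboratory, the plan accepts that reference limits can differ between laboratories, and for most liver outputs it adjusts for this. Tables 2.7.4-11 to -14 and the over-time plots do not. Conversion to SI units makes the units the same but does not remove differences between assays or reference ranges.

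Two things are at stake.

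- **Means.** One source supplies PA patients only, so an equal mix of laboratories in the two columns cannot be assumed. If laboratories also read at different levels, a difference in raw means can arise without a drug effect.
- **Plots.** Where laboratories have different ULNs, two dots at the same height can stand for different degrees of abnormality. This needs no imbalance between arms.

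Alkaline phosphatase stands apart because raw units are the only scale on which the plan reports it.

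**Working it through.** The SAP gives no figure to reproduce: it states no ULNs, no number of laboratories, and no patient numbers by study or laboratory. The arithmetic below shows only how the mechanism works and how far it could go.

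**Assumed inputs (none from the SAP)**

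- Two laboratories, A and B. ULN at A is 40 U/L. B reads k times A, and its ULN is scaled alike (k = 1, 1.25 or 1.5).
- No drug difference: mean ALT is 0.70 x ULN at Day 0 and 0.80 x ULN at Day 3 in both arms.
- Half of the AL patients are tested at B. In PA the share is larger by d (0 to 30 percentage points).
- Each child is tested at the same laboratory throughout.

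**Formulas**

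- Mean ULN in an arm with share p at B: 40 x [(1 - p) + p x k].
- Spurious PA minus AL difference in raw means: mean multiple of ULN x 40 x d x (k - 1).
- Spurious difference in change from Day 0: (0.80 - 0.70) x 40 x d x (k - 1), one eighth of the Day 3 figure.

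Example with k = 1.5 and d = 30 points: Day 3 gives 0.80 x 40 x 0.30 x 0.5 = 4.80 U/L. Mean ULN is 56 in PA and 50 in AL, a ratio of 1.12.

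| k | d (points) | Day 0, U/L | Day 3, U/L | Change, U/L | Relative, raw |
|---|---|---|---|---|---|
| 1.25 | 5 | 0.35 | 0.40 | 0.05 | 1.1% |
| 1.25 | 10 | 0.70 | 0.80 | 0.10 | 2.2% |
| 1.25 | 20 | 1.40 | 1.60 | 0.20 | 4.4% |
| 1.25 | 30 | 2.10 | 2.40 | 0.30 | 6.7% |
| 1.5 | 5 | 0.70 | 0.80 | 0.10 | 2.0% |
| 1.5 | 10 | 1.40 | 1.60 | 0.20 | 4.0% |
| 1.5 | 20 | 2.80 | 3.20 | 0.40 | 8.0% |
| 1.5 | 30 | 4.20 | 4.80 | 0.60 | 12.0% |

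With d = 0 or k = 1 every entry is 0. On the value/ULN scale the difference is 0 throughout. If B instead reads a fixed 5 or 10 U/L higher, the raw difference is that offset times d (0.25 to 3.0 U/L for d = 5 to 30 points), and the difference in change is 0.

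**Where ULN scaling would mislead.** Suppose the ULNs are 40 and 60 only because the reference populations differ, and the assays read alike. Raw means then carry no artefact. With 80% of PA and 50% of AL at the laboratory with ULN 60, mean 1/ULN is 0.2/40 + 0.8/60 = 0.01833 in PA and 0.5/40 + 0.5/60 = 0.02083 in AL. The ratio is 0.88, so value/ULN would be 12% lower in PA for no biological reason.

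**Plots.** With ULNs of 40 and 60, the plan's 3 x ULN line lies at 120 U/L in one laboratory and 180 U/L in the other. A dot between these heights exceeds 3 x ULN in the first and not in the second. The axis as worded does not tell the reader which applies.

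**The case against.** The strongest reply is that the plan already handles what matters.

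- **Tests.** Every planned liver comparison with a p-value is scaled to the local ULN. A reader might infer that pooling raw units inflates a false-positive rate. It does not, because no test is planned on raw means.
- **Time course.** A reader might also infer that the ULN-scaled time course is missing. Tables 2.7.4-16 and -17 give five ULN classes for ALT and AST at Days 0, 3, 7 and 28 and at the highest value. Table 2.7.4-18 adds bilirubin and the combined criterion.
- **Self-check.** A laboratory artefact would show at Day 0, before any drug. The change rows in the same tables remove an additive shift fully and most of a proportional one.
- **Evidence.** The SAP does not show that assay calibration or laboratory mix differs. A different ULN does not by itself mean a different reading. That a laboratory difference will appear as a liver difference between PA and AL is therefore more than the document supports.
- **Figure shell.** The picture for Figure 2.7.4-5 is not available, so the axis reading rests on the text of Section 8.2.

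All of this stands, and it limits the point to descriptive outputs. It does not answer two things. The plots show individual values without changes or ULN multiples. Alkaline phosphatase has no ULN criterion, class table or E-Dish plot to fall back on, and no over-time figure either.

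**Conclusion.** The point holds as a limited inconsistency in descriptive outputs. The plan leaves its own ULN scale in Tables 2.7.4-11 to -14 and, by the wording of Section 8.2, in Figures 2.7.4-5 to -7. Raw means can differ between PA and AL without a drug effect, but only if assay calibration and laboratory mix both differ. For the plots, differing ULNs alone are enough to make equal heights stand for unequal multiples of ULN.

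The real size cannot be determined from the SAP; the U/L figures above rest entirely on assumed inputs. The gap is clearest for the over-time plots and for alkaline phosphatase. The planned liver tests are not affected by this choice of scale.

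**What to change.** - **Section 8.2 and Figures 2.7.4-5 to -7:** plot each value divided by its local ULN. Draw reference lines at the plan's own thresholds: 1.5, 3, 5 and 10 x ULN for ALT and AST, and 1.5, 2 and 3 x ULN for total bilirubin.
- **Tables 2.7.4-11 to -14:** beside the raw units, add the same statistics for value/ULN and its change from Day 0.
- **Keep the raw units in the tables,** because ULN scaling can itself mislead when ULNs differ only through the reference population. Showing both scales lets the reader see whether they agree.

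The cost is a change of SAP wording, longer tables and revised figure shells. The ULNs for ALT, AST and total bilirubin are already needed for Tables 2.7.4-16 to -18; only the alkaline phosphatase ULN has to be read in as well.

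This does not cure the lack of stratification by study when a source with PA patients only is pooled with comparative data. That also affects the ULN-scaled tests and needs its own remedy.
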